### Data analysis

Data analysis will be conducted using both intention-to-treat and per-protocol approaches. A per-protocol analysis will utilize data from both ANC providers and their clients only if the provider was working in a clinic in the intervention arm and received the novel training on PCC for FGM prevention. Data from newly employed ANC providers in the intervention arm or from providers moving from an intervention to a control clinic will be excluded. No imputation of missing data will be performed.

A CONSORT flow chart describing excluded data and loss-to-follow up will be presented. Data analysis will be done using STATA 16 (StataCorp Inc., College Station, TX, USA) statistical analysis software.

At baseline, descriptive statistics will be used to compare client and clinic characteristics in the intervention versus control arms. Two-level regression models, with first ANC visit clients as the first level and ANC clinics as the second level, will be fitted. The ANC provider level will not be included since there is generally a low number of providers per ANC clinic in the study setting and it will not be ethical to collect data connecting provider and client. The region/county level will also be excluded given the low number of regions/counties per country and to limit the complexity of the multilevel models.

The primary study outcomes include the delivery of PCC on FGM using the “ABCD” approach by ANC providers measured from responses from validated patient and provider assessment measures that use the four constructs of the operational definition of person-centered communication [18]. As well as a health systems intervention package availability within ANC clinic and its use by ANC providers composite score defined as “health facility preparedness score” to provide FGM prevention and care services.

The secondary self-efficacy outcome will be assessed based on a score calculated from a validated tool for measuring general self-efficacy [19]. Interpersonal communication skills will be measured using a standardized questions on interpersonal communication while knowledge, attitude and practice skills on FGM prevention and care will be measured from a modified KAP questionnaire used in the formative research. Feasibility, acceptability, fidelity and coverage of interventions will be measured during the process evaluation. Unintended harms will be recorded and assessed in compliance with the study SOPs.

To determine the impact of the Level one intervention component, changes from baseline to month 3 in the intervention arm will be analyzed (Fig. 3). Analysis of change from month 3 to month 6 in the intervention arm will be used to determine the impact of the training on PCC for FGM prevention. At month 6, comparison of study primary, secondary and intermediary endpoints between the intervention and control arms will assess the impact of the complete intervention package. Both crude and adjusted Odds Ratios (OR) will be presented.

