**Fig. 1 Fig1:**
[figure not shown]
Staggered intervention implementation

The Level one intervention will be initiated in both study arms at baseline (month 0) while the Level two intervention will be initiated at month 3 in the intervention arm only. The Level one intervention aims to improve health facility preparedness to provide FGM prevention and care services. It seeks to passively strengthen the health workforce knowledge and skills to provide treatment and care for FGM complications and to not perform FGM.

In contrast, Level two intervention is an active approach where ANC providers from the intervention sites will receive a novel training package that aims to strengthen their interpersonal communication knowledge, skills and self-efficacy to communicate in an effective, empathetic and sensitive way with their patients. The training package comprises of diverse participatory adult learning methods such as values clarification exercises; storytelling sessions; interactive games using visual training aids and handouts; and demonstrations and role plays which simulate a variety of clinical situations in which FGM is discussed as well as viewing and discussing an animated video which depicts the life of a midwife who becomes an advocate for change to end FGM.

These training activities aim to develop the person-centered skills of health care providers to enable them discuss beliefs about FGM during a clinical consultation, encourage self-reflection to challenge existent FGM beliefs and support and empower women to abandon the practice. During the training ANC providers will be trained on how to deliver a standardized “ABCD” approach for PCC i.e. “Assess” clients’ views on FGM, address and challenge their “Beliefs”, explore the possibility of “Change” and with client, “Decide” on the next steps to be taken. In doing so, it is anticipated that the patient will be empowered to own and move forward with her decisions. The delivery of this “ABCD” approach for PCC on FGM prevention will be one of the primary outcomes of the study.

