### Sampling and randomization procedures

Randomization will be done at region/county level. All sampled ANC clinics will be paired based on average number of new ANC clients in November/December 2019, and then randomized into intervention and control arms on a 1:1 basis using STATA. The clinics will be blinded as to study arm allocation although ANC providers invited for the training on PCC for FGM prevention at month 3 may infer that their clinics are in the intervention arm. All ANC client participants will be blinded to study arm allocation of their ANC clinic.

For the process evaluation, sites will be selected based on responses from the month 3 data collection to identify sites that are complying with the level one intervention component. A convenience sample of six ANC providers and six new ANC clients from these clinics will be identified.

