### Data collection

Data collectors in all countries will be trained by standardized training developed by WHO with WHO participation and supervision. Similarly, data collection will have regular supervision and monitoring. To ensure high participation, participating sites will be notified in advance on planned data collection dates. Data management with regards to data entry, coding, security, and storage, including any related processes to promote data quality are detailed in the study operations manual. Quantitative data will be collected at three time points in the intervention arm: baseline, month 3 and month 6; and at two time points in the control arm: baseline and month 6. All data collection will be conducted using structured questionnaires pre-programmed into hand-held tablets. Quantitative data collection instruments will include a screening tool for ANC providers to assess their socio-demographic information (SCR); a questionnaire assessing their FGM-related practices, skills, and attitudes (HCP); an exit questionnaire (EXT) administered to first ANC visit clients to assess their exposure to level one intervention components as well as their perception of and satisfaction with the ANC visit encounter as relates to counselling for FGM prevention provided through the ABCD approach (Table 2). All data collection tools will be translated into local languages, tested and validated in the three countries.

**Table 2 Tab2:** Respondents and data collection tools at different study time-points

Respondent	Data Collection Tool	# to be Interviewed	Time-Point
Cluster Randomized Trial			
ANC providers	**SCR Questionnaire**	30 in each arm	**Intervention:** Baseline **Control:** Baseline
	**HCP Questionnaire**	30 in each arm	**Intervention:** 0, 3, 6 months **Control:** 0, 6 months
New ANC clients	**EXT questionnaire**	300 in each arm	**Intervention:** 0, 3, 6 months **Control:** 0, 6 months
Process Evaluation			
ANC providers	**In-depth interviews**	6	6 months
New ANC clients	**In-depth interviews**	6	6 months
Health facility	**Health facility checklist**	30 in each arm	0, 3, 6 months

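### The primary PCC-delivery outcome draws partly on self-report by trained providers who may infer their arm; the blinded client exit questionnaire should be its only source

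*Protocol article*

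**What the plan says.** - **Outcome source.** Under Data analysis, PCC delivery using the ABCD approach is one of two primary outcomes, "measured from responses from validated patient and provider assessment measures". Provider answers are thus a named source alongside client answers.
- **Instruments.** Under Data collection, the client exit questionnaire (EXT) covers the visit "as relates to counselling for FGM prevention provided through the ABCD approach". The repeated provider questionnaire (HCP) covers providers' practices, skills and attitudes. The other provider form (SCR) is a socio-demographic screen, so HCP is the evident source of the provider responses.
- **Training.** Under Study design, in the text following Fig. 1, "ANC providers will be trained on how to deliver a standardized" ABCD approach. This happens at month 3, in the intervention arm only.
- **Blinding.** Under Sampling and randomization procedures, clinics are described as blinded, although "ANC providers invited for the training on PCC for FGM prevention at month 3 may infer that their clinics are in the intervention arm". For clients the statement is unqualified: "All ANC client participants will be blinded to study arm allocation of their ANC clinic".
- **Model.** Data analysis describes two-level models "with first ANC visit clients as the first level and ANC clinics as the second level". It adds: "The ANC provider level will not be included since there is generally a low number of providers per ANC clinic". Data linking a provider to a client will not be collected.
- **Numbers.** Sample size gives 30 clinics and 300 first-visit clients per arm in each country, for a 10% difference and 10% non-response. Tables 1 and 2 give 30 providers per arm.

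**The concern.** The trial's second primary aim is to show that training improves the counselling clients receive. A provider taught four named steps three months earlier, and then asked about her practice, may answer from the training or say what she thinks is expected. Control providers do not receive that training. The two arms' provider reports can therefore differ even if consultations do not. Validation of the instrument does not protect against this, because the problem is differential reporting by arm, not poor measurement in general.

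Clients are the recipients of the counselling, are blinded, and are the respondents on whom the trial was sized. At stake is whether a positive primary result can be read as a change in counselling. With provider self-report inside the primary outcome, a sceptical reader has a ready alternative explanation.

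**Working it through.** **1. The sample size is a client count.** The article states 300 clients in 30 clinics per arm (10 per clinic). Significance level, power, control rate and intracluster correlation (ICC) are not given in the article, which is not itself a fault here. I read 10% as 10 percentage points and assume a two-sided 5% level and a binary outcome, since odds ratios are planned.

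n per arm = n(two proportions) × [1 + (10 − 1) × ICC] / 0.90

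- Control 5%, power 80%, ICC 0.10: 141 × 1.90 / 0.90 = 298
- Control 5%, power 90%, ICC 0.05: 188 × 1.45 / 0.90 = 303
- Control 10%, power 90%, ICC 0: 266 / 0.90 = 296
- Control 30%, power 80%, ICC 0.05: 356 × 1.45 / 0.90 = 574

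So 300 can be reached under some assumptions and not others. It can be neither confirmed nor called wrong.

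**2. What each source can detect.** Power = Φ[(d − 1.96 × SE0) / SE1], with d = 0.10, SE0 = √[2p̄(1 − p̄)/n] and SE1 = √{[p0(1 − p0) + p1(1 − p1)]/n}.

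- Clients: 300 × 0.90 = 270 responders, 9 per clinic. With ICC 0.05 the design effect is 1 + 8 × 0.05 = 1.4, so n = 270 / 1.4 = 192.9.
- Providers: n = 30, one per clinic on the planned numbers, with no deduction for non-response.

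Example at control 10% against 20%:

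- Clients: SE0 = 0.0364, SE1 = 0.0360, z = 0.80, power 79%.
- Providers: SE0 = 0.0922, SE1 = 0.0913, z = −0.88, power 19%.

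| Assumed control rate | Clients, 270 per arm, ICC 0.05 | Providers, 30 per arm |
|---|---|---|
| 2% | 97% | 33% |
| 5% | 91% | 25% |
| 10% | 79% | 19% |
| 20% | 62% | 14% |
| 30% | 54% | 12% |
| 45% | 50% | 12% |

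For 80% power, 30 providers per arm need a difference of about 31 to 36 points (control 10–45%). A continuous provider score would give other figures; the article does not fix the scale.

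**3. The two possible readings.**

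- *Sources combined.* If provider report has weight w and trained providers over-report by b points, the arm difference moves by w × b with no change in counselling. Both inputs are assumptions: 0.25 × 10 = 2.5; 0.25 × 20 = 5; 0.5 × 10 = 5; 0.5 × 20 = 10 points. If a spurious 5-point shift were carried into the client-level test (270 per arm), that test would be significant about 18–42% of the time (control 10–30%, ICC 0–0.05).
- *Sources separate.* The client measure is unaffected. The provider measure is still primary, still exposed to differential reporting, and rests on 30 respondents per arm.

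Each reading leaves a problem, though a different one.

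**The case against.** **Combination is not stated.** The article names measures in the plural and uses the term composite score only for the other primary outcome, facility preparedness. Separate analysis fits the text at least as well, and scoring rules may sit in the full protocol or analysis plan. This stands. A reader might infer that the client measure is diluted by averaging, or that half of any reporting shift reaches the result; the article supports neither. The shifts in the working are illustrations only.

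**The model gap may be condensation.** The provider-level secondary outcomes also have no described model, so the two-level sentence is probably not a full list of analyses. With one provider per clinic, a clinic-level analysis needs no provider–client link. This also stands. A reader might call the provider data incompatible with the planned analysis, but the article shows only that they fall outside the model and sample size it describes.

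**Knowledge of allocation is an inference.** The protocol says trained providers may infer their arm, not that they know it. Nothing shows that HCP uses ABCD terms or that control providers have never met them. The direction of bias is expected rather than proven, since training can also make people more critical of their own practice. So the claim is that bias is likely, not that it is established.

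**Clients also self-report.** EXT records perception and satisfaction, and hearing both sides of a consultation is a reasonable choice. That supports keeping both instruments. It does not support giving primary status to the respondents who were trained in the behaviour being scored.

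**Conclusion.** The point holds in a limited form. As written, a primary outcome draws on self-report by providers who, in one arm only, have been trained in the behaviour being scored and may infer their allocation. A blinded client source for the same outcome is already being collected. Differential reporting in favour of the intervention is likely; its size cannot be derived from the article.

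The problem survives either reading of the text. Combined sources may carry reporting bias into the primary result. Separate sources leave a primary measure resting on self-report, with about 12–33% power for the 10-point target against 50–97% for clients. Those figures assume control rates of 2–45%, a two-sided 5% level, a binary outcome, and ICC 0.05 with 10% non-response for clients. The article does not support a claim that the planned primary result is biased by any particular amount, or that the analysis contradicts itself.

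**What to change.** State under Data analysis that the primary PCC-delivery outcome is taken from the client exit questionnaire (EXT) at month 6 alone and compared between arms in the clients-within-clinics model. State that provider-reported delivery (HCP) is a secondary outcome, analysed at provider or clinic level, reported in its own right and not combined with the client measure.

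Both instruments, the visit schedule and the 300 clients per arm stay as they are. Provider knowledge, skills, self-efficacy and attitudes remain covered by the secondary aims.

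The cost is that provider-reported delivery loses primary status. It is also more than an editorial change. Redefining a primary outcome is an important amendment, which Ethical considerations says must go to the WHO ethics review committee and the in-country review boards. It should be made before month-6 outcome data are examined.

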A health facility assessment will be conducted at baseline, month 3 and month 6 in both intervention and control arms using a health facility checklist (CHK), which will assess compliance to the level one intervention component using an observational checklist as well as a short set of questions for health facility managers. The observation will assess dose and fidelity of the level one intervention component. The questions for the facility managers will assess catchment population, number of ANC providers, number of ANC clients seen per month, as well as number of staff meetings and supervisory visits held. It will also assess the facility’s environmental context regarding any pro- or anti-FGM activities targeting its catchment population.

Qualitative data in the form of in-depth interviews (IDIs) among a convenience sample of ANC providers and first ANC visit clients will be conducted at month 6 in the intervention clinics as described above. The IDIs will explore the acceptability, feasibility and other motivational/de-motivational factors that might influence intervention implementation. The IDIs will also be used to explore acceptability and appropriateness of the intervention as well as assessing respondents’ agency, perceptions of service delivery and any perceived impact of PCC on their FGM-related values/attitudes. The IDIs will be guided by an interview guide (Supplementary File 1).

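### The stated month-6 comparison between arms does not include the baseline outcome, although it is collected in both arms; the adjustment covariates and the primary estimate are not stated

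*Protocol article*

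**What the plan says.** On measurement, the Data collection section gives the provider and client questionnaires a baseline round in both arms. For the intervention arm it says "Quantitative data will be collected at three time points in the intervention arm: baseline, month 3 and month 6". Controls are surveyed less often, but still before any intervention: "at two time points in the control arm: baseline and month 6". Table 2 agrees. The checklist has the same baseline in both arms: "A health facility assessment will be conducted at baseline, month 3 and month 6 in both intervention and control arms".

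On analysis, the Data analysis section uses baseline between the arms only descriptively: "At baseline, descriptive statistics will be used to compare client and clinic characteristics in the intervention versus control arms". The change from baseline to month 3, and from month 3 to month 6, is analysed in the intervention arm alone. The one between-arm effect analysis, intended to show the effect of the full package, is worded "At month 6, comparison of study primary, secondary and intermediary endpoints between the intervention and control arms". The next sentence adds "Both crude and adjusted Odds Ratios (OR) will be presented". The models are two-level, clients within clinics, and no covariates are listed.

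The section on sampling and randomization pairs clinics on the volume of new clients, not on any outcome.

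**The concern.** As described, baseline outcomes enter the two analyses that have no control group and are absent from the one that does. The control arm's baseline round, 300 client interviews per country (half of the 600 control clients in Table 1) plus 30 provider interviews, has no stated inferential role.

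At stake are precision and the handling of chance imbalance. Each country has 30 clinics per arm, and pairing on volume does nothing direct to balance baseline outcomes. Lasting differences between clinics therefore stay in the noise of the month-6 contrast, and any chance imbalance in them carries partly into the estimate. It would also be cleaner to fix the choice between crude and adjusted results before month-6 data are seen.

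**Working it through.** **The plan's own figure.** The Sample size section gives 300 clients per arm per country for a 10% difference with 10% non-response. It cannot be reproduced, because alpha, power, control rate and ICC are not given. Some assumed sets match it: 5% vs 15%, two-sided 0.05, 80% power and ICC 0.10 give 141 × 1.9 / 0.9 = 298. Others do not: 30% vs 40% at 80% power needs 356 / 0.9 = 396 even with no clustering. ICC and control rate are therefore treated as assumptions below.

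**Inputs from the article.** 30 clinics and 300 clients per arm, so 10 clients per clinic, or 9 after 10% non-response; 30 providers per arm, one per clinic (Table 1).

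**Client outcomes.** Each round interviews new first-visit clients, so the only baseline value available for the outcome is the clinic's mean. With m = 9 and cluster autocorrelation c (the correlation of a clinic's true level between the two rounds), the correlation of clinic means is r = c × m × ICC / (1 + (m − 1) × ICC). Adjustment reduces variance by r². Assuming c = 0.6-0.8:

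| ICC | 1 + 8 × ICC | 9 × ICC / (1 + 8 × ICC) | r | Variance reduction |
|---|---|---|---|---|
| 0.01 | 1.08 | 0.083 | 0.05-0.07 | under 1% |
| 0.05 | 1.40 | 0.321 | 0.19-0.26 | 4-7% |
| 0.10 | 1.80 | 0.500 | 0.30-0.40 | 9-16% |

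**In power terms.** Effective n per arm is 270 / [(1 + 8 × ICC)(1 − r²)]. For 10% vs 20%, two-sided 0.05, c = 0.8:

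- ICC 0.01: 88.2% without baseline, 88.3% with it.
- ICC 0.05: 78.8% and 81.5%.
- ICC 0.10: 68.1% and 75.6%.

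The r² rule is exact for linear models and approximate for odds ratios.

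**Provider scores.** With one provider per clinic, assumed r = 0.5 gives 0.5² = 25% and r = 0.7 gives 0.7² = 49%. In equivalent clinics, 30 / (1 − 0.25) = 40 and 30 / (1 − 0.49) = 59 per arm. This needs the same provider at both rounds.

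**Chance imbalance.** The standard deviation of the observed baseline difference is √[2p(1 − p)(1 + 9 × ICC) / 300], with m = 10.

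- p = 10%, ICC 0.05: √(2 × 0.09 × 1.45 / 300) = 0.0295, a 95% range of about ±5.8 points.
- p = 30%, ICC 0.10: √(2 × 0.21 × 1.90 / 300) = 0.0516, about ±10.1 points.

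These ranges include sampling noise, which does not persist. With equal variance at both rounds, the expected carry-over to month 6 is r times the baseline difference. For m = 10 and c = 0.6-0.8, r is 0.21-0.28 in the first case and 0.32-0.42 in the second. Even an imbalance at the edge of the range would carry over about 1.2-1.6 and 3.2-4.3 points, against a target of 10.

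**The case against.** The strongest reply is that this is a condensed article. A master protocol exists, the figure titled as the data analysis plan is not shown, and covariate lists usually belong in an analysis plan. Adjusted odds ratios are promised, and nothing excludes baseline from them. That stands against a stronger reading which a reader might infer: that the analysis is fixed as post-only and the baseline information is lost. The documents do not establish this. It does not remove the point, because the article does assign baseline its uses, and the randomised contrast is not among them.

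A reader might also infer bias. Randomisation makes the month-6 contrast unbiased, and its standard error already covers chance imbalance. What is open is precision and the correction of the imbalance that actually occurs.

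The gain may also be small, and this too stands. The clinic baseline is a noisy mean of about ten women. Both primary outcomes may be near floor at baseline, since the package is first distributed at month 0 and the ABCD approach is taught at month 3. That is an inference; no baseline rates are given. The 40-59 equivalent clinics cannot be read as a gain for the trial as a whole: they concern provider scores only, on an assumed correlation.

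Finally, the article anticipates newly employed and moving providers and plans no imputation, so requiring each provider's own baseline score would drop replaced providers. A clinic-level fallback avoids this.

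**Conclusion.** The point holds as one of efficiency and clarity, not validity. The stated month-6 comparison does not include the baseline outcome, and the promise of adjusted odds ratios does not settle whether it will be used or which estimate is primary.

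For client-reported outcomes the size is modest under the assumed ICCs of 0.05 and 0.10 and cluster autocorrelation of 0.6-0.8, and nil in practice at ICC 0.01 or at floor. For provider scores it could be substantial, conditional on re-interviewing the same providers and on the assumed correlation. None of the ICCs, autocorrelations or correlations is given in the documents. The change is worth making because the data are already planned.

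**What to change.** State that each month-6 between-arm model includes the baseline value of the outcome being compared:

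- client outcomes: the clinic's baseline proportion or mean;
- facility preparedness: the clinic's baseline score;
- provider scores: the provider's own baseline score where the same provider is re-interviewed, otherwise the clinic's baseline score, so that replaced providers stay in the intention-to-treat analysis.

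Name this adjusted estimate as primary and keep the crude one as supportive, before month-6 data are seen.

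The cost is one model term and one degree of freedom per model, with no new data collection. The clinic-level fallback gives up some of the correlation for replaced providers, and outcomes at floor at baseline will gain little.

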### Study design

The proposed study is a hybrid, type-2, effectiveness-implementation research using a cluster randomized trial design [11]. The intervention being tested will involve a novel training for ANC providers to enable them to deliver person centered communication on FGM prevention while the health systems strengthening approach being evaluated includes making available health policies/directives, guidelines, posters and clinical tools which aims to prepare the health facility as an enabling environment for ANC providers to deliver FGM prevention and care services. A process evaluation will be conducted to explore ‘how’ and ‘why’ the intervention package achieves its intended results. The study design, methodology and analysis plan conform to the 2010 Consolidated Standards of Reporting Trial (CONSORT) checklist [12] while the proposed process evaluation conforms to the Consolidated Framework for Implementation Research (CFIR) recommendations [13].

The study interventions will target ANC clinics and ANC providers but will not affect the routine ANC services offered. Since we are proposing a dual testing of the effectiveness of a novel training and health systems strengthening approach, implementation of the study intervention components will follow a staggered approach (Fig. 1). The control and intervention arm will both receive Level one intervention which comprises of passive distribution of Ministry of Health directive or policy to health facilities on FGM prevention and care, WHO FGM clinical guidelines, clinical handbook on FGM and information and educational material in the form of posters to be hung to at the health facilities. The intervention arm will have ANC providers receive a novel person-centered communication training package on FGM prevention defined as the Level two intervention.

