## Discussion

While efforts to eradicate FGM have been ongoing for decades, there is lack of clear evidence on what works to prevent the practice and on the potential role of the health sector in this process [7]. A recent evaluation of a social norm change intervention showed promising results using community engagement strategies to address underlying social norms supportive of FGM [20]. A systematic review of health sector interventions found evidence from eight sub-Saharan Africa countries (Burkina Faso, Egypt, Ethiopia, Somalia, Kenya, Mali, Nigeria, and Senegal) on what activities and strategies the health sector could take to address FGM. These ranged from classroom didactic training, media communication, outreach and advocacy, as well as informal adult education [21]. These studies however, lacked scientific rigor; with majority using pre-and post-test assessments, lacking a comparison group or standardized measures, having follow-up periods that were too short to demonstrate impact, and not adequately controlling for contextual factors.

There is also lack of literature on the effectiveness of health system strengthening approaches towards FGM prevention. Another recent review exploring policy, training and service delivery interventions within the health sector found promising initiatives that have led to changes in attitudes among health care providers working with FGM affected populations [22]. However, there is lack of clear evidence from the health sector on what works to foster sustainable behaviour change. A systematic review of studies on the effectiveness of health systems strengthening strategies for other health issues found that educational meetings, trainings on educational outreach, practice facilitation, use of local opinion leaders, audit and feedback, and tailored interventions led to improvements in the health workforce capacity and service delivery, critical building blocks of health systems [23]. Analysis of the effect of the health system strengthening package in this study will, therefore, provide additional evidence to build on existing literature.

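### The month-6 randomised comparison estimates the training effect given Level one, not the complete package, while the training aim is tied to an uncontrolled before-after change

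*Protocol article*

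**What the plan says.** **Design.** The Study design section of the protocol article states: "The control and intervention arm will both receive Level one intervention". The text with Fig. 1 adds the timing. Level one starts "in both study arms at baseline (month 0) while the Level two intervention will be initiated at month 3 in the intervention arm only".

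**Mapping of contrasts to questions.** The Data analysis section names three:

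- Level one: "To determine the impact of the Level one intervention component, changes from baseline to month 3 in the intervention arm will be analyzed".
- Training: "Analysis of change from month 3 to month 6 in the intervention arm will be used to determine the impact of the training on PCC".
- Package: the month-6 comparison of endpoints "between the intervention and control arms will assess the impact of the complete intervention package".

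**Data waves.** Under Data collection, client and provider surveys in the intervention arm run at "baseline, month 3 and month 6; and at two time points in the control arm: baseline and month 6". The facility checklist differs: "A health facility assessment will be conducted at baseline, month 3 and month 6 in both intervention and control arms".

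**The concern.** The second primary aim asks whether PCC training improves delivery of prevention counselling. Clinics are randomised, and the only planned intervention difference between the arms at month 6 is the training. The randomised contrast therefore answers that aim directly, but the plan gives it another label and answers the aim from one arm without a control.

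Two conclusions are at stake. The between-arm result would be reported as the effect of Level one plus training when it holds only the training part. The training result would carry any background trend, any Level one uptake that continues after month 3, and any effect of repeated surveys on providers. The article itself, in its Discussion, lists among the weaknesses of earlier studies "majority using pre-and post-test assessments, lacking a comparison group or standardized measures".

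**Working it through.** **Inputs from the protocol article.** Level one in both arms at month 0; training in the intervention arm only at month 3 (Study design and Fig. 1 text). Client and provider surveys at 0, 3 and 6 months in the intervention arm and at 0 and 6 months in the control arm (Data collection, Table 2). Per country and arm, 30 clinics and 300 clients, with a 10% non-response allowance and a 10% target difference between arms (Sample size).

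**Plan's own figures.** Table 1 reproduces: 300 × 3 waves = 900, 300 × 2 waves = 600, total 1500. The 300 per arm cannot be reproduced, because the article gives no alpha, power, control rate or ICC. The point does not depend on it.

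**Step 1: what each contrast estimates.** Let b be the baseline level, L1 the Level one effect, and L2 the training effect on top of Level one. T1 and T2 are all other change in months 0–3 and 3–6; T2 includes any Level one effect that grows after month 3.

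| | Month 0 | Month 3 | Month 6 |
|---|---|---|---|
| Intervention | b | b + L1 + T1 | b + L1 + T1 + T2 + L2 |
| Control | b | clients and providers not surveyed | b + L1 + T1 + T2 |

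| Contrast | Plan's label | What it equals |
|---|---|---|
| Month 6, between arms | complete package (L1 + L2) | L2 |
| Month 3 to 6, intervention arm | training (L2) | L2 + T2 |
| Baseline to month 3, intervention arm | Level one (L1) | L1 + T1 |
| Baseline to month 6 change, difference between arms | none given | L2 |

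The package label is wrong whenever L1 is not zero. The two single-arm labels are right only if T2 = 0 and T1 = 0 respectively.

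**Step 2: examples with assumed values (percentage points).**

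- L1 = 5, L2 = 10, no background change: the package effect is 15; the month-6 arm difference is 10.
- L1 = 10, L2 = 0, no background change: the package effect is 10; the month-6 arm difference is 0.
- L1 = 5, L2 = 0, T2 = 10: the month 3 to 6 change is 10 although the training does nothing; the month-6 arm difference is 0.

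**Step 3: how often drift alone would look like a training effect.** Assumptions that are not in the article: ICC 0.05, cluster autocorrelation (CAC) 0.8, two-sided 5% test, month-3 rate p of 10% or 30%, L2 = 0, drift d. Clients per clinic: m = 300/30 × 0.9 = 9.

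Variance of the change = [p(1−p) + (p+d)(1−p−d)] × [ICC(1−CAC) + (1−ICC)/m] / 30.

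The second bracket is 0.05 × 0.2 + 0.95/9 = 0.1156; divided by 30 it is 0.003852. The chance of significance is Φ(d/SE − 1.96).

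| Drift d | p | First bracket | SE | d/SE | Chance significant |
|---|---|---|---|---|---|
| 0.05 | 0.10 | 0.0900 + 0.1275 = 0.2175 | 0.0289 | 1.73 | 41% |
| 0.05 | 0.30 | 0.2100 + 0.2275 = 0.4375 | 0.0411 | 1.22 | 23% |
| 0.10 | 0.10 | 0.0900 + 0.1600 = 0.2500 | 0.0310 | 3.22 | 90% |
| 0.10 | 0.30 | 0.2100 + 0.2400 = 0.4500 | 0.0416 | 2.40 | 67% |

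Holding the variance at the undrifted rate, 2p(1−p), gives 24% to 48% and 70% to 97%. The table is preferred because it uses the rate at each wave.

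**The case against.** **The valid contrast is already planned.** The month-6 comparison covers primary and secondary endpoints, intention to treat is specified, and the sample size rests on a difference between arms. This stands. The right estimate will be produced, and the fault is in which question it is said to answer. But the mapping is explicit for a primary aim, so it is not a detail left to a fuller document.

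**A reader might infer that the training conclusion must be wrong.** The documents do not support that. The month 3 to 6 change is confounded, and the article gives no size for any drift. If T2 is zero, the conclusion is right.

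**A reader might infer that the preparedness score will show almost no arm difference and be misread as failure of the package.** That does not follow. The score also covers use of the package by providers, which training could change. Only the Level one contribution cancels.

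**A reader might call the month-6 contrast free of all bias.** That is too strong. Intervention providers answer an extra questionnaire at month 3 and control providers do not, so any effect of that survey is part of the contrast. Each wave interviews first-visit clients, so for client measures it could act only through providers. This is a minor caveat.

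**Level one may barely move ABCD counselling.** ABCD is taught in the training, and Level one is passive distribution of materials. If L1 is small for that outcome, the wrong label changes the number little. This is fair, but the label still claims something the design cannot show.

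**The Discussion comparison should not be pushed far.** This trial has a randomised comparison group; the weakness lies in the single-arm analyses only.

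**Conclusion.** The concern holds for the mapping. From the article's own design statements, with no outside figure, the month-6 between-arm difference estimates the training effect given Level one and cannot estimate the complete package. Assigning the training effect to a single-arm change leaves the second primary aim resting on a confounded contrast when a randomised one is available. The baseline to month 3 analysis of Level one has the same weakness, and there the design offers no randomised alternative.

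The size is illustrative. The chance of a spurious training effect is about 23% to 41% for a 5-point drift, which is half the target difference, and about 67% to 90% for a 10-point drift. These figures depend on the assumed drift, ICC, autocorrelation and base rates; the mapping error does not. Fig. 3 is not shown, so whether it repeats the error cannot be judged.

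**What to change.** Revise the paragraph in Data analysis that assigns contrasts to questions, and Fig. 3 if it says the same:

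1. State the month-6 between-arm comparison by intention to treat as the primary estimate of the PCC training effect given Level one. Use the baseline data already collected in both arms, by adjustment or as a difference in change from baseline.
2. Label the intervention-arm changes from baseline to month 3, month 3 to 6 and baseline to month 6 as uncontrolled, descriptive before-after analyses.
3. Remove the claim that the between-arm comparison measures the complete package. State that the design gives no randomised estimate of Level one or of the full package.
4. Note the month-3 client and provider survey in the intervention arm only as a minor caveat to the between-arm contrast.

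The cost is a change of wording. No new data, visits or clinics are needed.
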